### Procedures

#### TB care provided in both groups.

Routine TB care is provided per the China National TB Guideline in both groups, where passive case finding is practiced. Patients self-present or are referred to the TB clinic at the County Hospital when they seek care for TB-related symptoms. TB diagnosis is based on X-ray examination, sputum smears and clinical assessment. Confirmed TB patients are treated in the TB Clinic of County Hospitals based on the WHO DOTS regimens for drug-sensitive TB. Those who are diagnosed with multi-drug resistant (MDR) TB are referred to prefecture level TB designated hospitals.

#### Usual care.

Usual care, i.e., the routine TB care provided in the National TB program, is provided in the control group, and no active case finding activities will be provided.

#### Intervention.

In the intervention group, in addition to usual care, we will implement an ACF campaign among all eligible participants in Year 1 (Fig 3). Prior to the visit, village social workers and village doctors will conduct door-to-door visits to recruit participants and obtain their informed consent. We will drive the mobile van to the village, and equip an AI-facilitated digital radiography (DR) machine and refrigerator on the van on a mutually agreed date. On the day, all eligible participants will be invited to complete a brief questionnaire regarding basic demographic information, medical history, smoking status and TB related symptoms, and then are invited to have their DR examined in the van. Based on digital chest X-rays, the AI software will identify TB assumptive participants who may have active TB, suspected TB or healed TB. In the first month of implementation in each county, one township hospital radiologist will facilitate the X-ray examination, double-check all results of the AI software, and make the final recommendation for presumptive TB. This process will be recorded to adjust the threshold score used by AI in each county. After the first month, the township hospital radiologist will still accompany the mobile clinic to help evaluate X-ray results if AI suggests for other lung diseases such as pneumonia or lung cancer, to minimize the risk of missing possible TB cases. Those who are presumptive of TB based on either DR examination or TB-related symptoms, i.e., any chronic cough over two weeks, hemoptysis, fever, night sweats, chest pain or unexplained weight loss, will be asked to produce a single on-site sputum. These villagers are also asked to take two specimen boxes for the collection of night and morning sputum. All staff are trained for good quality sputum sample collection, storage and transportation. Medical nebulizer inhalation will be provided to those who can not provide good-quality sputum. Sputum samples, either collected on the day or delivered by village doctors within 48 hours, will be stored in the refrigerator on the mobile van and transported back to the County Hospital daily for sputum testings, including smear microscopy, culture and GeneXpert assay. We will employ a sample mixing approach which has been validated in our previous publication [13]. Bacteriologically confirmed TB is defined by a positive result from any of the above sputum tests based on WHO and China National TB Program guidelines. Participants who are bacteriologically negative but have abnormal X-ray result or TB symptoms are referred to the county hospital for clinical assessment by a panel committee consisting of three senior doctors based on China National TB guideline for the diagnosis of clinically confirmed TB. All diagnosed TB patients, either bacteriologically or clinically confirmed, will be notified by the village doctor within 48 hours and referred to the County Hospital for standard WHO DOTS regimens per national guidelines.

**Fig 3 pone.0316073.g003:**
[figure not shown]
Algorithm of active TB case finding in intervention group. a. TB Symptoms include chronic cough over 2 weeks, hemoptysis, fever, night sweats, chest pain or unexplained weight loss. TB = tuberculosis, DR = digital radiography.

#### Research activities apply to both groups:.

We will wait for a year (cleaning period) to ensure all TB patients identified in Year 1 complete the treatment. Due to the constraint of resources, we can not conduct ACF activities covering all villages in Year 3. Instead, we will conduct an epidemiological prevalence survey in the intervention and control groups at Year 3 using cluster-random sampling methods at the village level, adopted from WHO [14,15], targeting high-risk populations in both intervention and control groups, to compare the TB prevalence rates. Regarding the survey, we will apply the same active case-finding activities as outlined above in both intervention and control groups.

### Outcomes

Our primary outcome indicator is the prevalence rate of bacteriologically confirmed TB in Year 3 among the high-risk populations, including those 65 and older, those who are under 65 but have a history of tuberculosis treatment or have been in close contact with a person diagnosed with TB within the past three years, have been clinically diagnosed with diabetes, HIV, or have a background of working as a miner. According to WHO definitions, bacteriologically confirmed case is defined as having a positive test from any of the three tests (i.e., GeneXpert, smear or culture). Prevalence is estimated using a cluster-random survey among the high-risk populations to be conducted in both the intervention and control groups in Year 3. The numerator is the bacteriologically confirmed TB cases identified from the Year 3 prevalence survey plus TB cases reported from the National TB program, and the denominator is the number of high-risk populations who are permanent residents and reside in the area at the time of the prevalence survey. The numbers of numerators and denominators at the village level will be aggregated at the township level and calculated based on the WHO TB prevalence survey analysis guide to estimate the TB prevalence rate in the intervention or control group [14].

There is a list of secondary outcome indicators, which allow us to assess and evaluate whether our interventions could bring positive impacts on TB epidemic between the intervention and control groups: 1) prevalence rate of active TB of the high-risk populations, including both bacteriologically confirmed and bacteriologically negative but clinically confirmed cases, among the high-risk populations in Year 3. This indicator will be calculated based on findings from the prevalence survey in Year 3 estimated using the WHO TB prevalence survey guideline [14]; 2) notification rates of bacteriologically confirmed TB cases among the whole population in Year 3; and 3) notification rates of active TB cases, including both bacteriologically confirmed and clinically confirmed cases among the whole population in Year 3. Numerators of the two notification rates will include TB cases identified from our prevalence survey in Year 3 plus TB cases reported from the National TB Program, while both denominators include all adult permanent residents (i.e., those of 15 years and older) who reside in the intervention and control groups at the time of prevalence survey.

We will also collect costs from patient, health system and societal perspectives to conduct an incremental costing study. We will collect process indicators that include a) the proportion of bacteriologically confirmed cases identified by active case finding in the intervention group; b) the yield rate of our intervention, which is the number of bacteriologically confirmed cases per 100 persons screened using each strategy.

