#### Laboratory testing and clinical consultation.

The county hospitals will carry out laboratory testing according to the ‘TB Laboratory Testing Protocol’. Sputum smear test, GeneXpert test and sputum culture are carried out at the same time. Every five samples of sputum will be mixed for GeneXpert test to save costs. Mixed samples that are positive will be re-tested individually to confirm the positive case. Country hospitals will distribute the laboratory testing results to patients within 48 hours. All TB diagnoses will be recorded in the ‘Register of Newly Diagnosed Patients’ in the National TB Program Registry. Clinical diagnosis based on the clinical assessment will be performed by a group of senior doctors in county hospitals according to the National TB Classification Criteria (WS196–2017) and Diagnostic Criteria (WS288–2017) [19,20]. We will collect TB cases diagnosed and reported in the National TB Program in both intervention and control groups through the three years.

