#### Determination of the primary and secondary outcomes.

We will combine the TB cases identified from the Year 3 prevalence survey and TB cases reported from the National TB Program to determine the numerators of our outcomes. The data collection approach in Year 3 for the outcome evaluation will be the same as the ACF activities conducted in the intervention group in Year 1. We will use the TB diagnosis algorithm as defined in our ACF to determine the bacteriologically confirmed and clinically confirmed cases. We will also collect the routinely reported TB cases through the National TB Program for Year 3. We will collect the information of all registered permanent residents who reside in the village at the time of Year 3 survey to determine the relevant denominators.

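### The primary numerator adds Year 3 National TB Program reports to survey cases without limiting them to confirmed, high-risk, prevalent cases and without a count-once rule

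*Protocol article*

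**What the plan says.** All references are to the protocol article.

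- **Name of the outcome (Outcomes).** "Our primary outcome indicator is the prevalence rate of bacteriologically confirmed TB in Year 3 among the high-risk populations". A confirmed case is one where "bacteriologically confirmed case is defined as having a positive test from any of the three tests", the tests being GeneXpert, smear and culture.
- **Numerator (Outcomes).** "The numerator is the bacteriologically confirmed TB cases identified from the Year 3 prevalence survey plus TB cases reported from the National TB program".
- **Denominator (Outcomes).** "the denominator is the number of high-risk populations who are permanent residents and reside in the area at the time of the prevalence survey".
- **Period of the program cases (Determination of the primary and secondary outcomes).** "We will also collect the routinely reported TB cases through the National TB Program for Year 3".
- **How the sources are joined (same section).** "We will combine the TB cases identified from the Year 3 prevalence survey and TB cases reported from the National TB Program", and this is said to give the numerators of the outcomes in general.
- **Registration (Laboratory testing and clinical consultation).** "All TB diagnoses will be recorded in the" program's register of newly diagnosed patients.
- **Routine diagnosis (TB care provided in both groups).** It rests on X-ray and clinical assessment as well as sputum smear.
- **Secondary outcome 1, all active TB in high-risk people (Outcomes).** "This indicator will be calculated based on findings from the prevalence survey in Year 3".

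**The concern.** The words that make this a bacteriologically confirmed outcome are attached only to the survey term. The program term refers simply to TB cases, and routine program diagnosis includes disease without bacteriological confirmation. Nor does the program term require membership of the high-risk group, to which the denominator is restricted, or disease still present at the survey. Taking program reports for Year 3 adds cases notified over a period, some of whom may have finished treatment, to the cases a survey finds when it visits.

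The two sources also overlap. A person diagnosed in the survey is to be entered in the program registry, and the text says only that the sources are added or combined.

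Finally, secondary outcome 1 contains the primary outcome as a subset. Under Outcomes it is based on survey findings; the later section applies both sources to all outcomes. If the Outcomes section is followed to the letter, the narrower outcome could come out higher than the broader one.

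At stake is what the primary odds ratio estimates, and whether it is the contrast the trial was sized for. The Costing study draws on primary outcome data, so an unclear numerator carries over to it.

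**Working it through.** **1. The plan's own figure.** Inputs from Sample size: control 300 and intervention 150 per 100,000, intra-class correlation 0.001, 500 eligible people per village, 80% power, p < 0.05 (taken as two-sided).

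- Design effect: 1 + (500 − 1) × 0.001 = 1.499.
- Two-proportion formula without continuity correction, 0.0030 vs 0.0015: 15,662 per arm.
- 15,662 × 1.499 = 23,477 per arm; 23,477 / 500 = 46.95, so 47 villages. This agrees with the stated 47 villages and about 23,500 participants per arm.
- Power at 23,500 per arm (effective size 23,500 / 1.499 = 15,677): 80.0%.
- Expected cases: 23,500 × 0.0030 = 70.5 and 23,500 × 0.0015 = 35.25.

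The stated size is thus reproduced by a plain 300 vs 150 contrast, with nothing added from the program.

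**2. Equal addition in both arms (assumption).** The protocol gives no Year 3 program count for high-risk residents. For scale only, take X = 134 per 100,000, the two counties' whole-population notification rate (Study design and setting), and half of it, X = 67. The ratio is (150 + X) / (300 + X). Power uses the same formula and an effective size of 15,677 per arm.

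| X per 100,000 | Rates, intervention / control | Ratio | Power |
|---|---|---|---|
| 0 | 150 / 300 | 0.50 | 80% |
| 67 | 217 / 367 | 0.59 | 69% |
| 134 | 284 / 434 | 0.65 | 60% |

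**3. Proportional addition (assumption).** If program cases raise both rates by the same factor 1 + f, the ratio is 150(1 + f) / 300(1 + f) = 0.50. There is no dilution.

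**4. Every survey case counted twice (extreme case).** Rates become 300 vs 600 per 100,000.

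- The ratio stays at 0.50.
- The absolute difference doubles from 150 to 300 per 100,000.
- Expected counts go from 70.5 vs 35.25 to 141 vs 70.5.
- The approximate standard error of the log ratio, √[1.499 × (1/c₁ + 1/c₂)], falls from 0.253 to 0.179. That is a factor of 1/√2, with no new information behind it.

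**5. The two statements on secondary outcome 1.** Outcomes bases it on the survey. The determination section, headed for primary and secondary outcomes alike, combines survey and program cases. The two give different numerators unless one is read as qualifying the other, and the text does not say which governs.

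**The case against.** The strongest defence is that the wording is loose but the intention can be recovered.

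- **The program term is not unlimited.** It is restricted to Year 3, and the protocol counts numerators and denominators by village before aggregating to township, which implies a limit of place. A reader might call the program cases unrestricted; the document does not support that. This stands.
- **The outcome's name may carry the bacteriological and high-risk limits.** The same loose phrase serves the numerators of both notification rates, confirmed and active. Read literally, it would make those two outcomes identical, which cannot be meant. This stands as a plausible reading, so loss of bacteriological confirmation is the literal reading and not a certainty.
- **Double counting is not stated.** A reader might infer that survey cases are counted twice. The registration rule creates the overlap, but combining sources can mean a union of unique persons, the reference to routine reports may have been meant to leave survey cases out, and matching rules may sit in an analysis plan not shown. Only the absence of a stated rule can be claimed.
- **Adding register cases has a purpose.** The denominator is all resident high-risk people, so the register can supply cases among those who missed or refused the survey. This is a fair reason to keep a register term. It does not justify taking every case reported in Year 3 regardless of disease status at the survey.
- **A pull of the odds ratio toward 1 is not established.** It follows from equal additions; steps 3 and 4 show it need not occur.

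On the most generous reading, two things remain: Year 3 notifications are mixed with survey prevalence, and the sections disagree on secondary outcome 1. Neither is detail that a later analysis plan would ordinarily supply, because the protocol itself fixes the rule.

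**Conclusion.** The concern holds in this form: the primary numerator is badly fixed. It joins Year 3 program reports to survey cases without confining them to confirmed, high-risk residents who are cases at the survey, and it states no count-once rule although the sources overlap by design. Different reasonable readings give different sets of cases, and only a survey-type prevalence matches the planned 300 vs 150 per 100,000.

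The size and direction of the effect are unknown. The ratios of 0.59 and 0.65, with power of about 69% and 60%, rest on equal additions of 67 and 134 per 100,000, and those values are borrowed from a whole-population rate. Additions that differ by arm in other ways could move the ratio either way. Full double counting would leave the ratio alone and would inflate case counts, apparent precision and the absolute difference.

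**What to change.** Replace the numerator sentence with one definition based on unique persons. Count a person who

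1. belongs to the high-risk denominator,
2. is resident in a sampled village at the survey, and
3. is either bacteriologically confirmed by the survey, or on TB treatment at the survey date with bacteriological confirmation in the program register.

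Link the survey and program records and count each person once. Use the same rule for secondary outcome 1, adding clinically diagnosed cases, and bring Outcomes and Determination of the primary and secondary outcomes into agreement. Leave all other program reports to the two notification outcomes. Settle this before the Year 3 data are analysed.

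The cost is a change of wording plus linkage of two sources the trial already collects. The estimand is then again the one that was sized, so the calculation stays at 47 villages per group.

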#### Participants.

In each township, all permanent residents based on household registration who are 15 or older and reside in the village or township at the time of investigation become eligible if meeting one of the following criteria as high-risk population: 1) elderly (i.e., aged 65 and above), or 2) aged below 65 but with one of the following conditions: being patients previously treated for TB, or close contacts of a patient with a TB patient diagnosed within the last three years; having been clinically diagnosed with diabetes, HIV positive, or worked as a miner. All eligible participants must sign informed consent forms to be recruited. Residents who refuse participation will be excluded.

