### Recruitment, randomization and blinding

There are 23 townships and 255 villages in Xincheng and Xiangzhou county of Laibin city [17]. We will implement the ACF activities at the township level to avoid contamination among villages because township hospitals manage village doctors. We seek to recruit all townships of the two counties. After recruitment, the study statistician will use a custom-written computer program to randomize all recruited townships, stratified by county, assigning them to the control and intervention group in an overall 1:1 ratio (12 intervention vs 11 control) [18]. Then township/village doctors and county hospital staff in the intervention group will be invited to receive training about specific interventions in this project. After randomization is done at the township level, the statistician will then randomly select 47 villages, stratified by county, from each group for the Year 3 prevalence survey. The selection of villages for prevalence survey will be sealed and blinded to providers and investigators until the Year 3 prevalence survey to prevent any provider-related bias. We will seek written informed consent from each participant before enrollment, as we need to collect their health information, bio-sample (sputum) and test result for research purpose.

Due to the nature of the intervention, neither single nor double blindness procedure of the allocation of groups is applicable. However, we will blind the data analysts who process the end-point data for outcome assessment.

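### The primary denominator counts all resident high-risk people, survey cases can come only from those screened, and the eligibility text excludes refusers: the sections conflict, and on the literal reading attendance affects the result

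*Protocol article*

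**What the plan says.** Under Outcomes, the primary measure is the Year 3 prevalence of bacteriologically confirmed TB in high-risk people, with its lower term fixed as follows: "the denominator is the number of high-risk populations who are permanent residents and reside in the area at the time of the prevalence survey". Determination of the primary and secondary outcomes agrees: the team will collect information on "all registered permanent residents who reside in the village at the time of Year 3 survey to determine the relevant denominators". Neither section makes consent or screening a condition for being counted.

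The numerator has two sources: "The numerator is the bacteriologically confirmed TB cases identified from the Year 3 prevalence survey plus TB cases reported from the National TB program".

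The Participants section, under Eligibility criteria, requires signed consent and adds: "Residents who refuse participation will be excluded". It does not say whether refusers leave only the survey or the denominator as well. Recruitment, randomization and blinding ties data and sputum to consent ("We will seek written informed consent from each participant before enrollment, as we need to collect their health information, bio-sample (sputum) and test result") and states that allocation is open: "neither single nor double blindness procedure of the allocation of groups is applicable".

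Village counts are summed by township and "calculated based on the WHO TB prevalence survey analysis guide to estimate the TB prevalence rate in the intervention or control group". Statistical analysis then applies a beta-binomial model to the township totals. The protocol gives no expected attendance rate and names no correction for non-participation.

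**The concern.** A person who does not attend the Year 3 van cannot become a survey case. If that person still sits in the denominator, undiagnosed TB in him or her is recorded as absence of TB. The measured rate then mixes prevalence with attendance, and a model fitted to township totals cannot separate the two.

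Unequal attendance is plausible. Allocation is open. For intervention residents the Year 3 survey is a second offer of the van, and for control residents it is the first. Staff in intervention townships were trained and ran the earlier campaign. This could raise or lower attendance, so the shift could create an apparent effect or hide a real one.

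The sentence excluding refusers allows a different denominator, so the primary outcome can be computed in two ways that give different answers. The authors do separate screened people from residents elsewhere: the yield indicator under Outcomes is expressed per 100 people screened.

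**Working it through.** **1. The plan's own figure.** Inputs from Sample size: 300 and 150 per 100,000, intra-class correlation 0.001, 500 eligible people per village, 80% power, 5% level (taken as two-sided; one-sided would give 37 villages).

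- n = [1.960·√(2p̄(1−p̄)) + 0.842·√(p₁(1−p₁)+p₂(1−p₂))]² / (p₁−p₂)², with p₁ = 0.003, p₂ = 0.0015, p̄ = 0.00225, gives 15,662 per arm.
- Design effect: 1 + 499 × 0.001 = 1.499.
- 15,662 × 1.499 = 23,477; divided by 500 this is 46.95, so 47 villages.

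The stated 47 villages are reproduced, with all 500 registered eligible people per village contributing a result.

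**2. Measured rate under the all-resident denominator.** Let π be true prevalence, c attendance, and s the share of cases captured by the program whether or not the person attends. Take s as equal in both arms and attendance as unrelated to TB. Then:

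- measured rate = π × [s + (1−s)c]
- ratio with no true effect = [s + (1−s)c_int] / [s + (1−s)c_ctl]

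The documents give neither c nor s; every value below is an assumption.

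| Attendance, intervention vs control | s = 0 | s = 0.3 |
|---|---|---|
| 75% vs 85% | 0.75/0.85 = 0.88 | 0.825/0.895 = 0.92 |
| 65% vs 80% | 0.65/0.80 = 0.81 | 0.755/0.860 = 0.88 |

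At such low prevalence the odds ratio is practically the same as this ratio.

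**3. False-positive rate with 300 per 100,000 in both arms** (two-sided 5% test, normal approximation, 23,500 per arm, the plan's design effect of 1.499):

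| Attendance, intervention vs control | s = 0: odds ratio, error rate | s = 0.3: odds ratio, error rate |
|---|---|---|
| 80% vs 85% | 0.94, 5.8% | 0.96, 5.4% |
| 80% vs 90% | 0.89, 8.2% | 0.92, 6.5% |
| 70% vs 90% | 0.78, 19.2% | 0.85, 11.3% |

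**4. The reverse direction.** With a true halving and attendance of 90% in intervention vs 80% in control, s = 0 gives 135 vs 240 per 100,000, odds ratio 0.56 and power 57.5%. With s = 0.3 the odds ratio is 0.54 and power 65.4%.

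**5. Equal attendance of 80%.** With s = 0 the measured rates are 120 vs 240 instead of 150 vs 300. The odds ratio stays at 0.50, but power falls from 80.0% to 70.8%. With s = 0.3 power is 73.9%.

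**6. Screened people as denominator, 80% attendance.** There are 400 people per village; the design effect is 1 + 399 × 0.001 = 1.399; effective size per arm is 47 × 400 / 1.399 = 13,438; power is 73.7%. Restoring 80% power takes 15,662 × 1.399 / 400 = 54.8, so 55 villages per arm. If attendance is unrelated to TB, an attendance gap alone leaves the expected odds ratio at 1.

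**The case against.** A reader might infer that every refuser counts as TB-free and that the estimate is exactly the true effect multiplied by the ratio of attendance rates. The protocol does not support that. Program-reported cases enter the numerator, so a non-attender with a program diagnosis is counted. The pure attendance ratio is the limiting case s = 0, and it also needs attendance to be unrelated to TB. This part of the objection stands and is why the results above are given as a range.

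The exclusion of refusers may mean that they leave the denominator, in which case the bias from refusal does not arise. That is a possible reading, but the two sections defining the denominator do not adopt it. The conflict is therefore itself part of the point.

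Unequal attendance is not shown. The same case-finding activities apply in both arms in Year 3, and the selected villages stay sealed until then. Small gaps do little: five points move the odds ratio by about 6% at most in the scenario above, and large false-positive rates need gaps of about 20 points. This stands, and it limits the severity.

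Finally, the protocol defers detail to a later analysis plan and to a WHO guide, neither at hand. The absence of a weighting or imputation method is thus no fault in itself, and whatever adjustment the guide contains is neither credited nor assumed missing. But the denominator is not deferred: the protocol fixes it, and does so inconsistently.

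**Conclusion.** The point holds as a conflict between sections, with a bias that follows if the outcome definition is taken literally. Prevalence is then understated in both arms whenever attendance is incomplete and the program misses some of the cases among non-attenders. Unequal attendance moves the odds ratio in either direction. With no true effect the ratio is 0.88 to 0.92 for 75% vs 85% attendance, and 0.81 to 0.88 for 65% vs 80%, as s goes from 0 to 0.3. With equal attendance of 80% and s = 0, the ratio is unbiased and power is about 71% instead of 80%. All of this rests on assumed attendance rates, an assumed s common to both arms, and attendance unrelated to TB.

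It would go too far to conclude that a false intervention effect is expected: the document gives no attendance rates and the direction is open. Severity: should be fixed.

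**What to change.** - Reconcile the Participants section, Outcomes, and Determination of the primary and secondary outcomes, stating whether people who refuse or do not attend are in the denominator.
- Make the primary denominator the eligible high-risk residents actually screened in Year 3, with numerator cases from the same people, and state how program-reported cases are handled.
- Correct for non-participation by inverse-probability weighting or multiple imputation, using the enumeration data (age, sex, village, risk group) that the sponsor confirms are available for non-participants.
- Report participation by township and arm.
- Keep the all-resident denominator, with program-reported cases, as a sensitivity analysis.

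This is a change of wording and analysis. It cannot be assumed to need no new data: the protocol promises information on all residents but does not list these variables for people who decline, and it links collection of health information to consent.

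There are three downsides. Fewer people enter the denominator. Program cases among unscreened people leave the primary numerator. The estimate relies on participation being unrelated to TB given the covariates used. Compared with the current rule, little or no power is lost: at 80% attendance and 47 villages, 73.7% against 70.8% (s = 0) or 73.9% (s = 0.3), before any variance added by the weighting. It remains below the planned 80%.

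### The two Year 3 notification rates put survey cases from sampled villages over a whole-arm adult denominator, so numerator and denominator do not match and the rates track the primary outcome

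*Protocol article*

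**What the plan says.** The Outcomes section lists two notification rates for Year 3 in the whole population: one for bacteriologically confirmed TB (secondary outcome 2) and one for all active TB (secondary outcome 3). For the numerator it says "Numerators of the two notification rates will include TB cases identified from our prevalence survey in Year 3"; routinely notified cases from the national program are then added to these. For the denominator it says "both denominators include all adult permanent residents (i.e., those of 15 years and older) who reside in the intervention and control groups".

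The survey does not cover that denominator. The section on research activities in both groups explains that "we can not conduct ACF activities covering all villages in Year 3" and that the survey targets high-risk people. The randomization section has the statistician "randomly select 47 villages, stratified by county, from each group for the Year 3 prevalence survey".

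Two further statements bear on the definition. The section on determining the outcomes says the team will collect information on "all registered permanent residents who reside in the village at the time of Year 3 survey to determine the relevant denominators", which can be read as the surveyed villages only. The laboratory section says "All TB diagnoses will be recorded in the" National TB Program register.

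**The concern.** A notification rate normally describes what the routine system reports in a defined population. Here part of the numerator is found by research screening of a sample, while the denominator covers everyone in the arm. Three things follow.

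- The result is neither a notification rate nor a population rate. Survey cases come from roughly a third of the villages and only from high-risk residents, and nothing scales them to the whole arm.
- The Statistical analysis section aggregates outcomes to the township, but villages are drawn with stratification by county only. A township's rate therefore depends partly on how many of its villages were drawn.
- Survey-detected confirmed cases are a main component of the primary outcome. Adding them to outcomes 2 and 3 carries the primary result into two outcomes that a reader would take as evidence about notification. A drop could be reported when routine notification had not moved.

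In addition, if survey diagnoses are entered in the program register, adding survey cases to program cases could count the same person twice.

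**Working it through.** **The plan's own figure.** Two-sided 5% test, 80% power, 300 versus 150 per 100,000: 15,662 per arm. Design effect 1 + (500 − 1) × 0.001 = 1.499. Product 23,477, or 46.95 villages of 500, rounded up to 47. The sample size reproduces and is not affected by this point.

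**Inputs from the protocol article.** 255 villages in 23 townships; 12 intervention and 11 control townships; 47 surveyed villages per arm; 500 eligible people per village; prevalence 300 per 100,000, planned to halve; notification rate 134 per 100,000 in the two trial counties.

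**Assumptions.** Adults per village are not given, so 1,000 to 2,500 is used. Townships have equal average size. Everyone eligible takes part and the survey finds all prevalent cases. Routine notification is 134 per 100,000 in both arms.

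**Coverage.** Intervention 255 × 12/23 = 133.0 villages; control 255 × 11/23 = 122.0. Surveyed share 47/133.0 = 35.3% and 47/122.0 = 38.5%.

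**Survey cases.** Control 47 × 500 × 0.003 = 70.5. Intervention 70.5 with no effect, 35.25 if prevalence halves.

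**Rate per 100,000** = 134 + 100,000 × survey cases / (villages in arm × adults per village):

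| Scenario | Adults per village | Intervention | Control | Ratio |
|---|---|---|---|---|
| Prevalence halves, routine unchanged | 1,000 | 134 + 26.5 = 160.5 | 134 + 57.8 = 191.8 | 0.84 |
| Same | 2,500 | 134 + 10.6 = 144.6 | 134 + 23.1 = 157.1 | 0.92 |
| No effect | 1,000 | 134 + 53.0 = 187.0 | 134 + 57.8 = 191.8 | 0.975 |
| No effect | 2,500 | 134 + 21.2 = 155.2 | 134 + 23.1 = 157.1 | 0.988 |

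In the control arm, survey cases make up 57.8/191.8 = 30% of the numerator at 1,000 adults per village and 23.1/157.1 = 15% at 2,500.

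**Surveyed-village denominator.** Each surveyed control village adds 1.5 survey cases. At 1,000 adults the rates are 134 + 75 = 209 versus 134 + 150 = 284, ratio 0.74. At 2,500 they are 134 + 30 = 164 versus 134 + 60 = 194, ratio 0.85. This reading removes the coverage mismatch but enlarges the survey's share.

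**Township level.** On average 47/12 = 3.9 or 47/11 = 4.3 villages per township are surveyed. As an illustration, take a township of 11 villages with 1,000 adults each at the control prevalence. Two surveyed villages add 2 × 1.5/11,000 = 27 per 100,000; six add 6 × 1.5/11,000 = 82. The TB burden is the same and the rates differ.

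**Sign of the no-effect imbalance.** The survey component alone has an expected intervention/control ratio of 11/12 = 0.917. With 7 to 12 villages per township (Eligibility criteria, Clusters) and 255 in all, the arms could hold anything from 144 intervention and 111 control villages to 123 and 132. The component ratio then runs from 111/144 = 0.77 to 132/123 = 1.07.

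**The case against.** **The outcomes are openly defined as composites.** The Outcomes section says what goes into the numerator and offers these rates as indicators of impact on the epidemic, not as measures of routine notification alone. In the scenario with ratios of 0.84 to 0.92, prevalence has truly halved, so the drop reflects a real reduction in detected TB. This stands in part: the ratio is not a false effect on TB. But the outcome is labelled a notification rate for the whole population, and on that label the drop would be misread.

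**A bias by arm even without any effect.** A reader might infer that sampling 47 villages from 12 versus 11 townships builds in a material difference. The documents do not support that. Adding survey cases raises the rate in both arms, the expected imbalance on the total rate is only about 1% to 3%, and its sign depends on village and adult counts that are not given.

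**Double counting as a fact.** A reader might also infer that survey cases are certainly counted twice. No passage says so, and matching records is ordinary detail for the analysis plan that the article announces. What stands is a risk: the two sources overlap by the laboratory section, and the outcome definition adds them.

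**The inputs are mixed.** The 134 per 100,000 is not stated to be for adults or for confirmed cases. For outcome 2 the routine term should be confirmed cases only; for outcome 3 the survey term should include clinically diagnosed cases. Both would enlarge the survey's share. Incomplete participation or a higher adult notification rate would shrink it. The range is therefore an illustration.

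**The denominator may mean surveyed villages.** The wording in the section on determining the outcomes allows this. It does not resolve the point, because the survey's share then grows.

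**Conclusion.** The point holds as a badly fixed definition of secondary outcomes 2 and 3. Read as written, cases from research screening of high-risk people in 35% to 39% of villages are placed, unweighted, over all adults of the arm, so the rates track the primary outcome and depend at township level on how many villages were drawn. With the planned halving of prevalence and no change in routine notification, the rate ratio would be about 0.84 to 0.92, an apparent fall of 8% to 16% that routine notification did not show. That range rests on assumed adult counts, equal average township size, full participation and an illustrative routine rate. The primary outcome and the sample size are untouched.

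**What to change.** Define both notification rates from National TB Program register cases in Year 3, one count per person. Flag and exclude cases first detected by the Year 3 survey. Use as denominator all adult residents of all townships in the arm. The flag is needed because survey diagnoses also enter the register, so dropping the survey term alone would not remove them. Make the denominator wording in the Outcomes section and in the section on determining the outcomes agree, and report survey-detected cases only in the prevalence outcomes.

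The cost is a change of definition, one flag in the register extract, and adult counts for townships as a whole rather than for surveyed villages only. The downside is that the survey may find people who would otherwise have been notified later in Year 3, which lowers routine notification where it took place. A sensitivity analysis should therefore be limited either to the part of Year 3 before the survey reaches each township, or to unsurveyed villages.
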